#### Secondary outcomes

##### Consumer dietary intake and consumption of promoted foods

Promoted food consumption was assessed using a previously-fielded brief quantitative food frequency questionnaire (QFFQ). Participants were asked to report the frequency of consumption of 22 foods/food groups over a 30-day period, choosing from eight categories ranging from “never” to “two or more times per day”. In addition to the QFFQ, a single quantitative 24 hour dietary recall was collected using a 5-step multiple pass methodology [41]. The dietary recall and QFFQ were collected on both weekdays and weekend days. The instrument was modified to include consumer food sources (i.e., supermarket, farmer’s market, corner store). Evaluation of consumer exposure to specific food sources will allow staff to track impact of local food policy initiatives (i.e., the proportion of calories consumed from urban corner stores). Dietary data will be analyzed using Nutrition Data System for Research (NDSR) software (version 11: Nutrition Coordinating Center, University of Minnesota).

##### Storeowner psychosocial variables to stock/sell promoted foods

Changes in psychosocial constructs toward the stocking and sales of promoted food items were assessed with the owners of participating corner stores. The Store Impact Questionnaire (SIQ) was adapted from an instrument previously used in former small store interventions [35,42] and was piloted before baseline data collection. The SIQ included sections on outcome expectations on sales of healthy foods and beverages, self-efficacy to stock, promote, and sell healthy foods and beverages, and intentions to sustain stocking and promotions on healthy items. Respondents were read a series of statements and asked to choose from one of five answers: Strongly Agree, Agree, Undecided, Disagree, or Strongly Disagree. Outcome expectations for promoted food sales was assessed with 16 questions (i.e., “Baked potato chips will sell well in my store”); outcome expectations on overall program impact was assessed with 18 questions (i.e., “If I receive a produce refrigerator for my store, fresh fruit/vegetable sales will increase”); 15 questions each were included to evaluate self-efficacy for stocking promoted foods (i.e., “I can stock 100% whole wheat bread in my store”) and intentions to sustain stocking of promoted foods (i.e., “I will stock frozen vegetables in my store after the program is completed”); and 6 questions assessed storeowners’ intentions to sustain pricing or communications promotions on the promoted foods after the program’s completion (i.e., “I plan to display BHRR promotional materials even after the program is completed”).

##### Sales of promoted foods

The SIQ captured promoted food sales by asking each participating store owner to estimate the number of units (i.e., cans, packages) of 15 key promoted foods sold in the store per day over the last 30 days. Additionally, a sales recall instrument, which has been used in earlier Baltimore-based studies, recorded store sales bi-monthly during the trial by asking each storeowner how many units of each promoted item were sold in the past 7 days [35]. A total of 12–15 weekly sales recalls were collected per store.

#### Other outcomes

##### Consumer body mass index

Anthropometric measurements were taken with adult consumer respondents wearing light, indoor clothing at baseline and post-intervention. Body weight was measured to the nearest 0.1 pound with Seca Model 880 portable electronic scale (Seca Corporation, Columbia, MD). Standing height to the nearest 1/8 (0.125) inch was measured with a Shorr Height Board (Shorr Productions, Olney, MD). Weight and height measurements were taken twice and averaged. If height measurements differed by ≥ 0.25 in or weight differed by ≥ 0.2 lb., a third measurement was taken and all 3 were averaged. These measures were used to calculate adult body mass index (BMI).

##### Household food security, food assistance, health beliefs, socio-demographics

The AIQ included the 18-item Household Food Security Survey (HFSS) module (Economic Research Service, USDA, 2008). The 18-item section included 10 questions that concern the experiences of adults and 8 concerning respondents’ experiences of providing food to children in their households. A section with 13 questions assessed participants’ health beliefs and attitudes and body image (e.g., “Healthy foods are expensive” and “I am satisfied with my weight”) using a 5-point Likert scale. Also included were questions regarding food assistance program participation over the past 12 months (e.g. SNAP, WIC), education level, income, employment, marital status, and housing.

##### Wholesaler sales of promoted foods

The participating wholesaler has agreed to provide promoted food sales records generated from wholesale databases. Reports will provide information on unit sales and revenue for each promoted food or beverage item overall and per participating store for each promoted food item from January to September 2013.

#### Process evaluation

Intervention implementation at the consumer-level was monitored twice monthly. Data collectors evaluated interactive sessions at each of the communications stores (n = 12) by reporting the number of consumers contacted through interactive sessions (reach), the number of different intervention components (i.e., giveaway, taste test, pamphlet, recipe card) delivered to each consumer at each interactive session (dose delivered), and how well each interactive session was delivered (fidelity) [34,43].

Intervention implementation at the store-level was monitored using a store environmental assessment form, modeled after the Nutrition Environment Measurement Survey-Stores (NEMS-S) instrument [44], to assess presence and placement of promoted food items and communications materials, and to provide additional commentary on contextual factors (e.g. cleanliness of store, expired items). The form also assessed whether the price was marked and if BHRR shelf labels or talkers were present and correctly identified the item. A wholesaler process evaluation form was used to track presence and visibility of promoted food items and BHRR logos. Pricing discount implementation was monitored using wholesaler electronic sales records and a weekly sales recall for small stores (12–15 sales recalls per store). At post-intervention, a separate intervention exposure questionnaire measured dose received, defined as the proportion of respondents who successfully recall exposure to a variety of specific intervention components/materials, for storeowners and customers.

### Analyses

Descriptive statistics will be used to compare the demographic characteristics of intervention and control participants at baseline using means or medians for continuous variables and proportions for categorical variables. A series of scales and scores will be developed to evaluate the impact of the intervention on food acquisition and psychosocial factors for consumers and storeowners [35,40]. All scales will be assessed for internal consistency and reliability using Cronbach’s alpha.

Key outcome variables will be store- and consumer- level outcomes, with treatment condition as the primary exposure variable. An intent-to-treat approach will be used to test study hypotheses. Multiple regressions will be conducted to assess program impact on consumer food-getting and food consumption, consumer BMI and food security, consumer and storeowner psychosocial variables, and small store purchasing and sales. All analyses will account for clustering (by store for individual-level outcomes and over time for store-level outcomes) using multiple regressions with clustered robust standard errors (e.g. Huber-White), generalized estimating equations (GEE), or multilevel modeling methods [45]. We will first test for interactions between pricing and communications intervention groups, and will remove the interaction term if effects are not found [46]. Statistical tests will be two-tailed with an alpha set at 0.05. Summary statistics will be used as appropriate for process evaluation data.

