## Methods

### Study design

BHRR is a 2x2 factorial RCT (Figure 1). Twenty-four small corner stores located in low-income census tracts of Baltimore City were randomized to one of four treatment groups: communications only (n = 6), pricing only (n = 6), combined communications and pricing (n = 6), or control (n = 6). Performance allowances in the form of healthy food discounts (10-30% off wholesale price) were directed from the wholesaler to the pricing only and combined intervention stores (12 stores total) at checkout for 6 months. In return for the discounts, storeowners were asked to stock selected healthier foods, and display communications materials and/or pass discounts to their consumers. The communications only and combined intervention stores (12 stores total) received in-store health communications, including taste tests, posters, and small refrigerators or freezers, to help stock and promote the sale of selected healthier foods. All customers of the participating corner stores were exposed to the 6-month intervention directed to that store. This study was approved by the Johns Hopkins Bloomberg School of Public Health Institutional Review Board.

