#### Store recruitment

The Johns Hopkins’ Center for a Livable Future provided study staff with GIS maps of small food stores that are located in low-income census tracts where greater than 75% of residents are African American. Study staff selected stores on the maps that met the following inclusion criteria: 1) in 2009, had average annual purchases of $5,000-20,000 from one or more participating food wholesalers; 2) not part of past store-based intervention trials in Baltimore [34,35]; and 3) were at least ¼ mile apart from each other. Recruitment of storeowners involved explanation of the purpose of the study, and distribution of recruitment materials explaining frequently asked questions and answers about the program. Korean-speaking research staff and translated recruitment materials were used in the recruitment of Korean storeowners. Staff approached 82 active stores for participation in the study; 34 storeowners refused to participate (e.g., citing a lack of time or not providing a reason), 16 asked staff to return when the owner was there, and 32 initially agreed to participate and out of those, 8 dropped out of the study prior to baseline data collection. Twenty-four storeowners completed surveys at baseline, 23 storeowners completed post-intervention surveys, and 22 storeowners completed the 6-month intervention in its entirety. Written informed consent was obtained immediately preceding any interviews and surveys.

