### Power calculation

Data used to calculate sample size were taken from a previous store-intervention study of African American adults in low-income inner city areas of Baltimore [35]. To account for clustering, we calculated sample size based on the intra-class correlation (ICC) formula [36] using a previous study’s psychosocial and food purchasing data. With a final, post-intervention sample of 12 consumers per store (n = 288 total) and 6 stores per groups, we will be able to detect an increase of 2 points in the food knowledge score, which implies that the respondent can correctly answer 2 additional questions related to food knowledge; an increase of 5 points for the self-efficacy score, which implies that the respondents feels confident to perform at least 1.3 additional healthful behaviors (i.e., choosing water instead of a sugar-sweetened beverage); and an increase in 3 points on healthy eating intentions, which implies that the respondent intends to perform at least 1 additional healthful behavior (i.e., purchasing 1% milk instead of whole milk). Using a conservative estimate of ICC for healthy and unhealthy food getting frequencies, we will be able to detect approximately 20 points increase in the healthy food getting frequency and a 20 point decrease in the unhealthy food getting frequency.

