### Randomization and blinding

To ensure comparison of treatment groups with similar characteristics, stores were stratified by WIC status and daily sales volume. Daily sales volume was calculated from the baseline unit sales of promoted foods in the past 30 days. Greater than or equal to 20 unit sales of promoted items per day was defined as large volume, while less than 20 unit sales per day was defined as low volume. Sales volume was used as a proxy for daily sales revenue, since storeowners were reluctant to share exact monetary estimates with research staff. Similarly, WIC status was used as a proxy for healthy food stocking, since stores carrying WIC must have a minimum required stock of certain healthy foods at all times. Thus, randomization was stratified by: high-volume stores with WIC; high-volume stores without WIC; low-volume stores with WIC; low-volume stores without WIC.

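### Huber-White and GEE errors are allowed for 24 randomised stores with no small-sample correction stated; run uncorrected, nominal 5% tests would operate at about 7-10%

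*Protocol article*

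**What the plan says.** The store is the unit of randomisation. The Study design section states: "Twenty-four small corner stores located in low-income census tracts of Baltimore City were randomized to one of four treatment groups", with 6 stores in each group. The Power calculation section plans the analysis set in the same terms: "With a final, post-intervention sample of 12 consumers per store (n = 288 total) and 6 stores per groups".

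For the analysis, the Analyses section says that clustering will be handled "using multiple regressions with clustered robust standard errors (e.g. Huber-White), generalized estimating equations (GEE), or multilevel modeling methods". It adds: "Statistical tests will be two-tailed with an alpha set at 0.05". On the factorial structure it says: "We will first test for interactions between pricing and communications intervention groups, and will remove the interaction term if effects are not found".

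The section does not say which of the three methods is primary. It does not mention a finite-sample variance correction, a reference distribution or degrees of freedom, either to adopt them or to rule them out.

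**The concern.** Cluster-robust (Huber-White) and GEE sandwich variances are justified when the number of clusters is large. Here there are 24 in all, and only 12 in any comparison of two arms. In their ordinary form these variances are too small on average with so few clusters. A normal reference also ignores the uncertainty in the variance estimate. Both faults make p-values too small and confidence intervals too short.

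Three features of this plan make that relevant.

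- The Study hypotheses section compares intervention stores with control stores and expects the largest gains in the combined arm. Contrasts of 6 stores with 6 stores are the natural way to examine that ordering, and they are the worst affected.
- The interaction test decides which model is reported, so its error rate carries into everything that follows.
- The three methods are offered as alternatives, but in their default forms they have different error rates on this design. An open choice among them lets the p-value depend on which is picked.

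**Working it through.** **Inputs.** 24 stores, 6 per arm (Study design). 12 consumers per store after the intervention (Power calculation). Two-sided alpha 0.05, interaction tested first (Analyses). The ICC value is not printed; the article says only "Using a conservative estimate of ICC for healthy and unhealthy food getting frequencies". I assume 0.01 to 0.10.

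**Step 1, the plan's own figure.** 24 x 12 = 288, which agrees with the Power calculation section. The article gives only the nominal 0.05 for type I error, so there is no achieved rate to reproduce.

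**Step 2, uncorrected sandwich with a normal reference.** Treatment is constant within a store. With equal store sizes the estimate is therefore a contrast of store means, and a GEE with exchangeable correlation gives the same estimate and the same sandwich variance as ordinary regression with Huber-White errors. That variance divides the squared store residuals by the number of stores instead of the residual df. With r = (residual df) / (stores used), the test statistic under the null is a t variable divided by sqrt(r), so

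type I error = P(|t_df| > 1.960 x sqrt(r)).

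| Test | df | r | 1.960 x sqrt(r) | Type I error |
|---|---|---|---|---|
| Main effect, 12 v 12 alone | 22 | 22/24 | 1.877 | 7.4% |
| Main effect, both factors in model | 21 | 21/24 | 1.833 | 8.1% |
| Interaction, four-arm model | 20 | 20/24 | 1.789 | 8.9% |
| 6 v 6 contrast with control | 10 | 10/12 | 1.789 | 10.4% |

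The variance of a store mean cancels, so the ICC does not enter this result.

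**Step 3, the usual partial correction.** Multiply the variance by G/(G-1) = 24/23 and refer to t on 23 df (critical value 2.069):

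type I error = P(|t_df| > 2.069 x sqrt(r x 24/23)).

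- Main effect: cut-off 2.023 on 22 df gives 5.5%; cut-off 1.977 on 21 df gives 6.1%.
- Interaction: cut-off 1.929 on 20 df gives 6.8%.
- 6 v 6 contrast: cut-off 1.929 on 10 df gives 8.3%.

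**Step 4, multilevel model with a normal reference and no df correction.** P(|t_20| > 1.960) = 6.4%. This ignores any truncation of the store variance at zero.

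**Step 5, simulation under the null.** The 24-store 2x2 design, 12,000 runs per setting, ICC 0.01, 0.05 and 0.10, with 12 consumers per store or 6 to 15 per store:

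| Method | Main effect | Interaction | 6 v 6 contrast |
|---|---|---|---|
| Sandwich, uncorrected, normal reference | 7.8-8.9% | 8.9-9.8% | 10.5-11.3% |
| G/(G-1) scaling, t on 23 df | 5.8-6.6% | 6.5-7.4% | 8.2-9.2% |

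A t test on store means, with df equal to stores minus store-level parameters, gave 4.8-5.5% across the three tests. The simulation agrees with the closed forms. Unequal store sizes make the sandwich results slightly worse.

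**The case against.** The strongest reply is that the article prescribes no uncorrected analysis. It names families of methods, and a condensed article commonly leaves variance corrections and degrees of freedom to the full protocol or SAP, which are not shown. A reader might infer that the trial's tests will run at 7-10%. The text does not support that, and silence on the correction is not by itself an error. This part of the objection stands, and it makes the size conditional.

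A second reply also stands: one of the three listed options is a multilevel model, for which the 7-10% range does not apply. So it would be wrong to say that every test in the trial is inflated to that degree. For main effects, which are what remains once a non-significant interaction is dropped, the common scaling with t on 23 df already brings the error near 6%.

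Two further inferences go beyond the document.

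- Since "stores were stratified by WIC status and daily sales volume", one might add three stratum terms to the model. A single simulated setting (ICC 0.05, unequal sizes) then gave 11.5-13.4% for uncorrected single-df tests. The Analyses section does not say that such terms enter the regression, so this figure is only illustrative.
- One might claim that the detectable differences are understated because they used normal quantiles. The Power calculation section does not say which quantiles were used, so this cannot be shown.

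Nor does the statement that "22 storeowners completed the 6-month intervention in its entirety" mean that only 22 clusters will be analysed, because the plan is intention-to-treat.

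What the objection does not remove is that the article lists as interchangeable three methods with different default error rates at this number of stores. Two of them, run in their ordinary form, give intervals that are too short.

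**Conclusion.** The point holds in conditional form. If Huber-White or GEE errors are used uncorrected with a normal reference, nominal 5% tests of consumer-level outcomes run at about 7-8% for main effects, 9% for the interaction and 10% for a 6 v 6 contrast with control. Scaling by G/(G-1) with t on 23 df leaves about 6%, 7% and 8%. An uncorrected multilevel model runs at about 6.4%.

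The closed forms assume equal store sizes and outcomes for which store means are roughly normal with equal variance. The simulations relax the equal sizes and hardly change with the ICC.

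This should be settled before analysis, since it bears on the interaction test and on the comparisons with control. It does not invalidate the design, and it is less than an essential correction, because the article permits a suitable method and excludes no correction.

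**What to change.** Name one primary method for consumer-level outcomes. A linear mixed model with a random store effect and Kenward-Roger or Satterthwaite degrees of freedom is preferable, and it is already within the options listed.

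If GEE or robust errors are kept, require a bias-reduced variance (Mancl-DeRouen, Kauermann-Carroll or CR2) with a t reference on stores minus store-level parameters: 24 - 4 = 20 df for the four-arm model. A robust variance for a contrast of two arms draws only on their 12 stores, so 10 df is the matching reference there.

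The cost is a sentence in the plan and a software option; the design and the data collection do not change. Intervals become somewhat wider. On 20 df the multiplier goes from 1.960 to 2.086, which is 2.086/1.960 = 1.06 times a normal-reference multilevel interval. Against the uncorrected sandwich interval for the interaction the ratio is about 2.086/1.789 = 1.17, which is the width that interval lacked.

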**BHRR study design.**

### Study hypotheses

The study tests the consumer-level hypotheses that, by the end of the 6-month intervention, customers of the 18 intervention stores (pricing only, communications only, and combined) will have, 1) greater increases in frequency of purchasing and consumption of the promoted foods than those at control stores, with the greatest increases among those consumers at combined intervention stores, and 2) greater increases in psychosocial factor scores relating to healthy food choices than those at control stores, with the greatest increases in the combined intervention stores. The study tests the store-level hypotheses that, by the end of the 6-month intervention, the 18 intervention storeowners will have 3) greater increases in sales and stocking of promoted foods compared to control stores, with the greatest increases in the combined intervention stores, and 4) greater increases in store owner psychosocial factor scores related to stocking and sales of promoted foods compared to control stores, with the greatest increases in the combined intervention stores.

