#### Consumer recruitment

A convenience sample of the first fifteen eligible customers/consumers that expressed interest in participating in the research study were recruited between May and September 2012 (total n = 360 consumers). Participants were eligible for the study if they: (1) were African American adults aged 21 or older, (2) lived within 0.25 miles of the store where they were recruited, (3) shopped in the store at least once a week, and (4) were the main food shopper for their household. All participants were interviewed outside of the stores where they were recruited, were explained the purpose of the study and signed a written informed consent form prior to interviews.

Both store owner and consumer respondents were compensated with $20 gift cards upon completion of each interview, which lasted approximately 1 hour.

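### The pricing-by-communications interaction is dropped after a low-powered non-significant test, so the data decide what the pricing and communications effects mean; the estimands should be fixed in advance

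*Protocol article*

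**What the plan says.** All of this is in the protocol article.

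- **Analyses** states the model rule: "We will first test for interactions between pricing and communications intervention groups, and will remove the interaction term if effects are not found". The same section says "Statistical tests will be two-tailed with an alpha set at 0.05", with no separate level for the interaction test. It describes the regressions "with treatment condition as the primary exposure variable" and does not say whether that is one four-level variable or two crossed factors.
- **Study design** allocates 24 stores equally, 6 to each of the four cells.
- **Study aims** asks for the impact of the two strategies both separately and combined. **Study hypotheses** predicts that all three intervention groups beat control, "with the greatest increases among those consumers at combined intervention stores", and makes the same prediction for storeowners.
- **Power calculation** works from this basis: "With a final, post-intervention sample of 12 consumers per store (n = 288 total) and 6 stores per groups". It lists detectable differences of 2 knowledge points, 5 self-efficacy points, 3 intentions points and about 20 food-getting points. It gives no power, SD, ICC value or contrast, and nothing for the interaction.

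**The concern.** The rule chooses the model by testing the same data that the model then describes. With the usual 0/1 coding of the two factors, the pricing coefficient means pricing alone against control (6 v 6 stores) if the interaction stays, and the marginal pricing effect (12 v 12 stores) if it goes. These are different quantities unless the effects add, and the reported intervals and p-values take no account of the selection step.

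What is at stake is the trial's main promise, evidence on each strategy alone and on both together. Non-additivity is a live possibility on the article's own account. Its Background cites a Dutch supermarket trial in which education alone had no effect on fruit and vegetable purchases, yet the largest increases came when it was added to a discount.

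**Working it through.** **1. What can be reproduced.** Only the counts: 12 × 24 = 288 final consumers; 15 × 24 = 360 enrolled; 288/360 = 0.80 retained. The detectable differences cannot be reproduced without SD, ICC and power.

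**2. Standard errors.** Let σ² be the variance of a store mean and v = σ²/6 the variance of a cell mean.

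| Contrast | SE | In units of σ | Interaction SE ÷ this SE |
|---|---|---|---|
| 12 v 12 main effect | √v | √(2/12) = 0.408 | 2.00 |
| 18 v 6, any intervention v control | √(4v/3) | √(4/18) = 0.471 | 1.73 |
| 6 v 6 pairwise | √(2v) | √(2/6) = 0.577 | 1.41 |
| Interaction | √(4v) | √(4/6) = 0.816 | 1 |

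SD and ICC cancel in the last column, so the ratios follow from the design alone.

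**3. Power of the interaction test.** Assumption: the stated differences (call each δ) have 80% power at two-sided 0.05, so δ = (1.96 + 0.84) × SE = 2.80 × SE. For an interaction of r × δ, the expected test statistic is 2.80 × r ÷ (ratio above).

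- δ for 6 v 6, r = 1: 2.80/1.41 = 1.98, power 51%.
- δ for 18 v 6, r = 1: 2.80/1.73 = 1.62, power 37%.
- δ for 12 v 12, r = 1: 2.80/2.00 = 1.40, power 29%.
- r = 0.5: 17% (6 v 6) down to 11% (12 v 12).
- r = 1.5: 84% (6 v 6) down to 56% (12 v 12).
- 90% power assumed instead, r = 1: 63% (6 v 6) down to 37% (12 v 12).

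Using the t distribution with 20 df (24 stores less 4 cells) both to set δ and to test the interaction gives the same 51% and 29%. To have 80% power, the interaction would have to be 1.41δ (6 v 6 reading) or 2δ (12 v 12 reading).

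**4. What the coefficient estimates after removal.** Let P be the effect of pricing alone and I the interaction. The marginal pricing effect averages P (no communications) and P + I (with communications), which is P + I/2. It equals the pricing-alone effect only if I = 0.

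**5. Behaviour of the whole procedure.** Simulation with normal store means, 6 stores per cell, at least 200,000 trials per scenario. Ranges run over the 6 v 6 and 12 v 12 readings of δ.

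- No effects at all: the pricing coefficient is significant in about 6.5% of trials, not 5%.
- Additive effects: the term is dropped in 95% of trials, the estimate is unbiased, and coverage is about 93.5%.
- Effect δ in combined stores only, so P = 0 and I = δ: the term is dropped in 49 to 71% of trials, and the pricing estimate then averages δ/2. The 95% interval covers the pricing-alone effect in 75 to 79%, and pricing is declared effective in 21 to 25%.
- Each strategy alone gives δ and combining adds nothing, so I = −δ: the term is dropped and both main effects are significant in 6 to 11% of trials. Under the additive model that reads as combined beating each single arm. Requiring both direct combined-versus-single contrasts to be significant makes that error in about 0.5%.

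**The case against.** Several stronger readings are tempting, and the article does not support them.

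- **That the interaction test has 30 to 50% power.** This is not a figure of the plan. It needs an assumed power, an assumed contrast and an interaction as large as the full detectable difference. The range in step 3 runs from 11% to 84%.
- **That the hypothesis about combined stores cannot be tested once the term is removed.** In the additive model, combined v pricing alone is the communications effect, and combined v communications alone is the pricing effect. Either can turn out null or negative, so the ordering can fail. It also needs no synergy: two positive additive effects satisfy it. What is assumed is additivity, not the ordering.
- **That the reported effects will routinely be the wrong ones.** This holds only if a material interaction exists. The 75 to 79% coverage belongs to an interaction as large as δ. The combined-only scenario is also more extreme than the article's own expectation that all three intervention groups beat control.
- **That a missed interaction will usually be reported as two effective strategies.** When only the combined stores benefit, the term is dropped and both main effects are significant in just 6 to 11% of trials.
- **That the planned contrasts are missing.** A condensed article may leave a contrast list to the full protocol or SAP, and treatment condition could mean four groups.

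There is also a real argument for the additive model. If each strategy adds the 6 v 6 detectable difference, the stated rule finds the pricing effect in about 96% of trials against 80% for the pairwise contrast. With 24 stores that matters.

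What survives is the rule itself. It is stated in the article, not left to another document. It takes a non-significant result from the design's least precise contrast as grounds for assuming additivity.

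**Conclusion.** The point holds in a limited form, as a should-fix. The removal rule makes the meaning of the pricing and communications effects depend on a pre-test that cannot establish additivity with 6 stores per cell. The standard-error ratios of 2 and 1.41 follow from the design and need no assumption beyond equal cell variances. The power figures are conditional on 80% power for the stated differences and on the size of the interaction.

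The harm ranges from small (additive effects, or no effects at all) to material (a real interaction of the detectable size). Which case applies is unknown, and the rule's own test is poorly placed to tell them apart. Once the term is gone, a claim that combined stores did best rests on an assumption the data have not supported.

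**What to change.** Delete the data-driven removal and name the estimands before the analysis. The marginal main effects (12 v 12 stores) may remain the main analysis, which keeps the efficiency of the factorial design. Whatever the interaction p-value, also report with 95% intervals:

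- the interaction;
- the four cell estimates;
- each single arm v control;
- combined v each single arm.

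Base any statement that combined stores did best on the two direct combined-versus-single contrasts, both of which should support it. State whether treatment condition enters as four groups or two factors.

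The change is a few sentences and needs no new data. Its price is precision for the direct contrasts. If effects are additive at the 6 v 6 detectable difference, both combined-versus-single contrasts are significant in about 69% of trials. The present rule drops the term and finds both main effects significant in about 91%. Reporting that wider uncertainty is the honest position for 24 stores.
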